**Figure 2 Fig2:**
[figure not shown]
**Statistical analyses procedure of the CORRA study.** CORRA: Comparison of the efficacy and safety of two starting dosages of prednisolone in early active rheumatoid arthritis, Pl: placebo group, V10: group starting with 10 mg prednisolone daily, V60: group starting with 60 mg prednisolone daily.

Statistical analysis will be performed using an intention-to-treat (ITT) approach. It is expected that 12-month results will be missing for less than 5% of the patients (dropout rate). In step one and two, missing radiographs after one year are substituted by randomly selected radiographs of patients of the placebo group (both replacements by the same patient), thus leading to conservative results for the PRED groups. In step three of the test procedure, missing values will be excluded from the analysis. A sensitivity analysis will be done for the effect of the replacement procedure (the random replacement will be repeated several times).

Analysis of the secondary outcome parameters will be performed by ITT using all available data. Continuous characteristics of the groups will be compared using analysis of covariance adjusting for baseline data. Analysis of categorical variables or proportions will be performed using the chi-square test. An additional repeated measures analysis will be done for all quantitative endpoints taken at several time points.

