### Sample size

It is assumed that progression of radiographic joint damage as measured by the SHS will be the same for both dosage levels of PRED. For sample size calculation we used data from the BeSt-study [9]. We thus assume an effect of 3.7 and a standard deviation of 7.5. Accounting for a 5% dropout rate, the effect will be 3.5. If 150 patients per group are included, a two sided t-test of superiority (α = 0.05) between one of the PRED groups and the placebo group will give a power of >0.95. Accepting a non-inferiority margin of 1.3 (one third of the known placebo-verum difference) for the difference in progression between the PRED groups, the one sided non-inferiority test in step three (at α = 0.025) will give a power of >0.80, if 149 patients per PRED group are included. The significance level of α = 0.025 was chosen according to the European Medicines Agency guidelines [25]. Thus, the final sample size has been set as 150 patients per group.

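### The step-three non-inferiority test drops patients without a one-year film, has no sensitivity analysis for them, and its sample size makes no allowance for losing them

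*Protocol article*

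**What the plan says.** The protocol article, under Blinding and statistical methods (text after Figure 2), opens with a general principle: "Statistical analysis will be performed using an intention-to-treat (ITT) approach". It expects fewer than 5% of one-year results to be missing. It then sets two rules for them. In steps one and two, "missing radiographs after one year are substituted by randomly selected radiographs of patients of the placebo group", and the article justifies this as conservative for the PRED groups. For the non-inferiority comparison, "In step three of the test procedure, missing values will be excluded from the analysis". One sensitivity analysis is named: "A sensitivity analysis will be done for the effect of the replacement procedure", carried out by repeating the random replacement.

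The Sample size section handles dropout once, by shrinking the superiority effect: "Accounting for a 5% dropout rate, the effect will be 3.5". The non-inferiority power of more than 0.80 is stated for a margin of 1.3 and one-sided α = 0.025, "if 149 patients per PRED group are included". The final size is 150 per group.

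**The concern.** In steps one and two, patients without a film are replaced, the choice is argued to be conservative, and its effect is tested by repetition. In step three they are removed, no argument about direction is given, and nothing tests the result. Removal is safe only if, given baseline SHS, a missing film is unrelated to progression. In a non-inferiority test, losing the worse outcomes from the lower-dose arm makes the arms look alike, which is the error the test should guard against.

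The sample size has the matching gap. Dropout was allowed for where patients are replaced, and not where they are taken out. Step three needs 149 per arm and 150 are randomised, so there is one patient to spare.

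Much depends on this step. The Discussion says that, if low-dose bridging compares with an effective high-dose bridging, a current treatment recommendation is confirmed.

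**Working it through.** **Inputs (Sample size; Blinding and statistical methods).** Effect 3.7, SD 7.5, margin M = 1.3, one-sided α = 0.025, target power 0.80, true V10–V60 difference 0, 150 randomised per arm, 5% missing (the article's upper expectation). Normal approximations are used; noncentral-t results differ by less than 0.003.

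**1. The superiority figures reproduce.** Dilution: 0.95 × 3.7 = 3.515, about 3.5. Power with 150 per arm, difference 3.5 and SD 7.5 is 0.98, in line with the stated >0.95.

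**2. The non-inferiority figure does not reproduce at the stated SD.** n per arm = 2σ²(1.96 + 0.8416)² / M².
- σ = 7.5: 2 × 56.25 × 7.849 / 1.69 = 522.4, so 523.
- σ = 4.0: 2 × 16 × 7.849 / 1.69 = 148.6, so 149.

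The stated 149 therefore implies an SD of about 4.0, which the article does not give. A gain from baseline adjustment would explain it only with a correlation of about 0.85, since √(1 − (4.005/7.5)²) = 0.845. That is not stated either.

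**3. Effect of exclusion on power.** 150 × 0.95 = 142.5, so about 142 evaluable per arm. Power = Φ(M / (σ√(2/n)) − 1.96).

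| n per arm | SD 4.0 | SD 7.5 |
|---|---|---|
| 150 | 0.804 | 0.323 |
| 149 | 0.801 | 0.321 |
| 142 | 0.782 | 0.309 |

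Keeping 149 evaluable needs 149 / 0.95 = 156.8, so 157 randomised per arm. At SD 7.5, 523 / 0.95 = 550.5, so 551.

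**4. Possible bias in the complete-case difference.** Assumption: a share p of V10 is missing and progresses d points more than V10 completers, while V60 loses no such patients. The difference is then understated by p × d.
- p = 0.05, d = 3.7 (the size of the planned placebo–PRED effect): 0.185 points; 0.185 / 1.3 = 14% of the margin.
- p = 0.10, d = 3.7: 0.37 points, 28% of the margin. This exceeds the dropout the article expects.
- To hide the whole margin at p = 0.05, d would have to be 1.3 / 0.05 = 26 points.

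**5. Error rate at the margin.** If the true difference among all randomised patients is 1.3, the error is Φ(0.185/SE − 1.96), with SE = σ√(1/142 + 1/150).
- σ = 7.5: SE = 0.878, error 0.040.
- σ = 4.0: SE = 0.468, error 0.059.

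The nominal level is 0.025.

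**6. Would placebo-film replacement help in step three?** No. Replacing 5% in both PRED arms turns a true difference of 1.3 into 0.95 × 1.3 = 1.235, a shift towards non-inferiority.

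**The case against.** *A reader might infer that step three breaks the ITT rule.* The document does not support that. It says "Analysis of the secondary outcome parameters will be performed by ITT using all available data", so here ITT evidently means analysis by randomised arm of those who have data. Excluding patients without a film fits that usage.

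*The different handling in step three can be defended.* Placebo-film replacement is conservative for superiority and anti-conservative for non-inferiority (item 6), so leaving it out of step three is reasonable. This stands. It does not explain why nothing took its place.

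*The direction of bias is unknown.* Nothing in the article shows that poorly controlled V10 patients leave. Lack of efficacy leads to a change of therapy within the study, and the Background mentions toxicity concerns with 60 mg, so selective V60 loss is as plausible. If dropouts in both arms behave like placebo, at equal rates, complete cases slightly overstate the V10 disadvantage, which is the safe direction. This stands, and is why the 0.19 is an illustration and not an estimate.

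*A reader might also infer that converging therapy goes unchecked because no per-protocol analysis is named.* The article plans a secondary analysis of the primary outcome adjusted for MTX dose, biologicals and later GC dose, and it describes the aim as comparing strategies. A per-protocol set may be defined in the full protocol or SAP, which are not shown. Its absence from the article is no defect.

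*The power lost through exclusion is small,* about 2 percentage points, and lower power makes a non-inferiority claim harder. Both are true. The larger shortfall comes from the SD.

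**Conclusion.** The point holds in limited form. The article fixes a complete-case rule for a confirmatory non-inferiority test and gives it no sensitivity analysis of its own. Below 5% missing, the likely bias is modest compared with the margin. Under the one-sided scenario above it is still enough to raise the error at the margin from 0.025 to 0.04–0.06. That figure depends on loss confined to V10 and a 3.7-point excess, both assumptions, and the bias could reverse.

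The sample-size part needs no assumption about who drops out. At the article's own 5%, about 142 per arm remain against 149 required, so power above 0.80 is not delivered: it is 0.78 at the SD of about 4.0 that reproduces 149, and 0.31 at the stated 7.5. It would be wrong to blame the exclusion for most of this. At SD 7.5 the power is already 0.32 with all 150 patients.

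**What to change.** - **Step-three analysis.** Replace exclusion with multiple imputation within arm for all randomised V10 and V60 patients, using baseline SHS and the DAS28 values already collected at each visit. Do not extend placebo-film replacement to this step.
- **Sensitivity analysis.** Add a delta-adjusted (tipping-point) analysis that worsens only the imputed V10 values, and continue until the conclusion changes. Stopping at a shift of 1.3 would be too weak: at 5% missing it moves the estimate by 0.05 × 1.3 = 0.065 points, 5% of the margin.
- **Power statement.** Restate step-three power for about 142 evaluable per arm, name the SD used, and reconcile it with the stated 7.5.
- **Per-protocol analysis.** If one is reported, treat it as supportive only.

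The analysis changes need wording and some programming, and no new data. A non-inferiority claim becomes slightly harder to reach. If the SD used was about 4.0, holding 149 evaluable would mean 157 randomised per arm, 7 more than planned. If it was 7.5, no small increase restores the stated power, and the statement itself has to change.

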## Methods/Design

### Trial design

CORRA is a multicenter, randomized, placebo-controlled, double-blind clinical trial conducted in 30 rheumatology practices in North Rhine-Westphalia, Germany. Most of these practices are members of the RheumaNetz Westfalen-Lippe, a local cooperation of rheumatologists in the eastern part of North Rhine-Westphalia. In total, 450 patients with early active RA will be randomized to receive one of two GC treatments (starting with 10 or 60 mg PRED, tapered down to 5 mg PRED within eight weeks) or placebo, each arm comprising 150 patients. The duration of the intervention is 12 weeks. In parallel, all patients start medication with methotrexate (MTX), at a usual dosage of 15 mg/week. The primary efficacy endpoint is radiographic joint damage after one year compared to baseline. Important secondary endpoints are the percentage of patients in remission, patient global assessment of disease activity, and changes of functional capacity. Safety monitoring is performed.

The study is approved by the local ethic committees Ethik-Kommission der Ärztekammer Westfalen-Lippe und der Medizinischen Fakultät der Westfälischen Wilhelms-Universität Münster (leading ethic committee: 2013-250-f-A), Ethik-Kommission der Ärztekammer Nordrhein, Dusseldorf, and Ethikkommission bei der Ärztekammer Niedersachsen, Hannover. It is registered at the European Union Drug Regulating Authorities (EudraCT: 2012-004074-25), at ClinicalTrials.gov (NCT02000336), and German Clinical Trials Register (DRKS-Nr: DRKS00004774). The principles of good clinical practice will be an essential component of the trial. It will be conducted in accordance with the Declaration of Helsinki. All patients will be required to give written informed consent before inclusion in the study.

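### Placebo replacement in steps one and two is conservative for PRED only under a condition the protocol does not state, and repeating the random draw cannot test that condition

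*Protocol article*

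**What the plan says.** The rule is in the Protocol article, Blinding and statistical methods, in the text after Figure 2: "In step one and two, missing radiographs after one year are substituted by randomly selected radiographs of patients of the placebo group". The article presents the consequence as following from the rule itself: "thus leading to conservative results for the PRED groups". The check named for it reads: "A sensitivity analysis will be done for the effect of the replacement procedure (the random replacement will be repeated several times". On the amount of missing data the same section says: "It is expected that 12-month results will be missing for less than 5% of the patients (dropout rate".

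The Sample size section makes the matching assumption: "We thus assume an effect of 3.7 and a standard deviation of 7.5", and then "Accounting for a 5% dropout rate, the effect will be 3.5". Dropouts are thus credited with no benefit.

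Nothing else in the article varies the assumption for steps one and two. Step three drops missing values, but it compares the two PRED arms. The adjusted secondary analysis of the primary outcome concerns methotrexate, biologicals and later glucocorticoid use. The repeated-measures analysis is for endpoints taken at several time points, whereas radiographs are taken only at baseline and one year.

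**The concern.** Whether the rule is conservative depends on how the PRED patients without a one-year film actually progress, compared with the placebo patients who supply the substitutes. Donors necessarily have a film. A PRED patient lost after treatment failure or intolerance need not resemble them. If such patients do worse than donors, and the placebo arm has no similar losses, the substitution hides progression in the PRED arm and favours PRED.

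Redrawing donors leaves this assumption where it was. Each repeat takes values from the same pool, so the results scatter around one centre. A stable set of redraws shows that the luck of the draw did not matter. It says nothing about whether placebo-like progression was a fair assumption.

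This matters because steps one and two open the hierarchy: without them the non-inferiority comparison is not reached.

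**Working it through.** **Inputs.** SD 7.5, effect 3.7, diluted effect 3.5, 150 per arm, two-sided α = 0.05 (Sample size, Trial design); missing below 5% (Blinding and statistical methods). The article gives no outcomes for dropouts, so the excess progression used below is an assumed range.

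**1. The plan's own figures.** Dilution: 0.95 × 3.7 = 3.515, stated as 3.5. SE = 7.5 × √(2/150) = 0.866. Power = Φ(3.5/0.866 − 1.96) = Φ(2.08) = 0.981, in line with the stated >0.95.

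**2. Direction of the bias.** Let m₁ and m₀ be the missing fractions in PRED and placebo, and d₁ and d₀ the mean excess progression of the missing patients over the placebo donors. Replacement understates mean progression by m₁d₁ in PRED and m₀d₀ in placebo. The bias in favour of PRED is therefore m₁d₁ − m₀d₀. With m₀d₀ = 0, the rule is conservative if d₁ < 0, neutral if d₁ = 0 and favourable to PRED if d₁ > 0.

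**3. Error in the PRED-favouring tail** (nominal 0.025) when the true all-patient difference is zero: 1 − Φ(1.96 − bias/0.866).

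| Missing PRED / placebo | Excess over donors | Bias | Error |
|---|---|---|---|
| 5% / 0% | 3.75 (0.5 SD) | 0.1875 | 0.041 |
| 5% / 0% | 7.5 (1 SD) | 0.375 | 0.063 |
| 10% / 0% | 7.5 | 0.75 | 0.137 |
| 8% / 2% | 7.5 in both arms | 0.06 × 7.5 = 0.45 | 0.075 |
| 5% / 5% | equal in both arms | 0 | 0.025 |

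Simulation with donor resampling gave 0.035 and 0.054 for the first two rows, 0.065 for the fourth and 0.025 for the fifth. A separate ANCOVA simulation with 5% missing in both arms and only the PRED dropouts worse gave 0.044 (3.7 points) and 0.070 (7.5 points). With placebo-like dropouts it gave 0.028 at 5% missing and 0.024 at 15%, so the level is held when the assumption is true.

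**4. What the redraws can show.** With 8 of 150 films replaced in one arm, the draw contributes an SD of (8/150) × 7.5/√8 = 0.14 points. With 8 in each arm it is 0.14 × √2 = 0.20. The centre does not move, so a bias such as 0.375 points is invisible however many redraws are made.

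**5. Tipping shift.** The smallest significant difference is 1.968 × 0.866 = 1.704. The shift at which significance is lost is (observed difference − 1.704)/m₁:

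| Observed difference | 5% missing | 10% missing |
|---|---|---|
| 3.5 | 35.9 | 18.0 |
| 2.5 | 15.9 | 8.0 |
| 2.0 | 5.9 | 3.0 |
| 1.75 | 0.9 | 0.5 |

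The 10% column exceeds what the plan expects. These values hold the SE at 0.866. A large shift also widens the PRED arm. At a shift of 30 and 5% missing, the PRED variance is 56.25 + 0.05 × 0.95 × 30² = 99.0, the SE is √((99.0 + 56.25)/150) = 1.017 and the threshold is 2.00, which equals 3.5 − 0.05 × 30 = 2.0. The value 36 then becomes about 30. The conclusion is the same.

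**The case against.** The other side has several good arguments.

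- **Usual meaning of conservative.** Giving missing PRED patients placebo outcomes removes any benefit credited to them, as the dilution to 3.5 shows. No single imputation rule protects against every mechanism. This stands as a description of intent. It does not make the unconditional wording correct.
- **Purpose of the redraws.** A single random replacement needs a check on its draw, and the article does not claim that the redraws test anything more. This stands, and the redraws should stay.
- **Condensed article.** An analysis plan not shown may contain further missing-data analyses. This also stands. The point is confined to what the article states: an unconditional label, and a check that cannot support it.
- **Mechanism of loss.** DMARD changes for inefficacy or side effects are allowed within the study, the intervention lasts 12 weeks, and analysis is by intention to treat. Stopping or switching treatment need not mean a missing film. Placebo patients lost for inefficacy are also given donor values, which pushes the other way. All of this stands.

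A reader might infer that the rule does inflate the error in favour of PRED. The article does not support that. The inflated rows above need missingness or deficits that are worse in PRED than in placebo, and nothing in the document shows either.

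A reader might also infer that the redraws would falsely confirm a marginal result. That does not follow either. A difference of 1.75 lies 1.75 − 1.704 = 0.046 above the threshold, or about 0.33 of a redraw SD of 0.14, so roughly 37% of redraws would lose significance and the fragility would show. The blind spot lies somewhat higher. A difference of 2.0 is about two redraw SDs above the threshold, so few redraws would lose significance, yet at 5% missing a shift of about 6 points would overturn it.

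**Conclusion.** The point holds in limited form. The label is conditional and the article states it without its condition. The sensitivity analysis it names varies only the draw and cannot test that condition.

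The size depends on the result. At an observed difference of 3.5 with 5% missing, the conclusion is robust: the tipping shift is about 36 points with the SE held fixed, and about 30 if the SE is allowed to grow. The point gains weight if the observed effect is nearer 2.0 (about 6 points at 5% missing), if more than 5% of films are missing, or if missingness is unequal between arms. A smaller effect is not far-fetched, since the article's Discussion itself considers that PRED may add little under treat-to-target care.

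The figures assume SD 7.5 and 150 per arm, and the excess progression of dropouts is an assumed range. They do not show that the trial is biased, only that the planned check could not tell.

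**What to change.** Keep the placebo replacement as the primary rule, and keep the redraws as a check on draw noise. Make two changes:

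1. **Add a delta-adjusted (tipping-point) series for steps one and two.** Give replaced PRED patients the placebo donor value plus 0, 2, 4, … Sharp score points, run each increment over the same set of redraws, and report the shift at which each step loses significance.
2. **Qualify the wording.** State that the rule is conservative provided PRED patients with missing one-year films progress less than the placebo donors, and neutral if they progress equally.

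A complete-case ANCOVA may be shown for description, but it does not test this bias. With a complete placebo arm and a true all-patient difference of zero, its bias is m₁d₁/(1 − m₁). At 5% missing and 7.5 points excess that is 0.375/0.95 = 0.395, against 0.375 under replacement, so it favours PRED slightly more.

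The cost is a few sentences and a few analysis runs on data already collected. The downside is that a borderline positive result may have to be reported as dependent on the missing-data assumption. A strong result would be shown to be robust, which the redraws alone cannot do.

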## Discussion

The most frequently used dosage of 7.5 to 10 mg PRED as a bridging treatment in early RA is a compromise between the good clinical short-term effect of GC and the attempt to minimize the risk of AE. However, the first months of RA are considered to be like a window of opportunity, with the best offer to change the course of the disease. This window of opportunity should be used to ‘hit hard and early’ (provide aggressive treatment as soon as possible) [14]. It may well be that higher dosages of GC, as used in the COBRA study [8] and the BeSt-study [9], have a higher impact on the outcome without a considerable increase of AE. The answer to this question would be highly relevant for the individual patient because of the increased possibility to induce a more favorable course of the disease. The immediate benefits for society in general and for the economic expenditures in particular are obvious.

The aim of our study is to test different treatment strategies rather than to evaluate the dose-dependent effect of PRED on the Sharp score. This means to find answers to two questions. Firstly, is it worthwhile to start with a high-dose PRED treatment in active RA patients, even if a treat-to-target approach is followed? Secondly, is there any difference between initially high and low PRED doses in the sense of benefit in radiographic progression? In the further course, there are many potential confounders, such as imbalanced MTX use, imbalanced GC use during weeks 13 to 52, and imbalanced use of biologics. These imbalances may flaw the immediate effect of the PRED bridging on the Sharp score, but have only a minor impact on the tested treatment strategies. The possible results of our testing procedure may clarify if high-dose PRED bridging is not superior to a placebo, then the disease modifying effect of PRED no longer plays a major role in a treat-to-target setting. If there is a significant difference between high-dose PRED bridging and placebo, and low-dose PRED bridging is not superior to a placebo, then high-dose bridging may be strongly recommendable. If a low-dose bridging compares to a significantly effective high-dose bridging, the EULAR recommendation of merely regarding the symptomatic effect of PRED is confirmed. If there are no differences between all three groups even with sufficiently imbalanced concomitant therapies, then only symptomatic effects of PRED should guide treatment decisions.

Of course, these results must be judged by considering other endpoints such as adverse events, clinical response to treatment, and patient-related outcomes. Therefore recommendations should take into account all these results. It is possible, depending on the results, that there may remain sufficient uncertainty and, therefore, that a confirmatory trial may be needed. Nonetheless, the primary endpoint should not be blurred by these short-term results because the focus lies on disease modification as measured by the Sharp score.

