Therefore, most rheumatologists rather use 7.5 to 10 mg PRED in the initial treatment of RA, increasing the dose in case of lack of efficacy, and tapering the dose over the following weeks to bridge the interval until DMARD become clinically efficacious. Unfortunately, there is insufficient data concerning this dosage schedule.

In order to shed further light on the best possible GC treatment strategy in early RA regarding both efficacy and safety, we have designed a study which may guide future treatment decisions.

The main aims of this study are: to compare the use of GC as a bridging therapy with placebo in a treat-to-target setting with DMARD, and to define the best out of two standard GC dosage regimens. Both aims are with regard to the progression of radiographic joint damage after one year compared to baseline.

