### Blinding and statistical methods

All participating rheumatologists and radiologists will be blinded against the interventions, thus assuring blinded assessment of outcome variables.

The primary endpoint is the progression of radiographic damage after one year compared to baseline (measured by the SHS). Analysis will be performed in three steps to compare the three groups (Pl: placebo group; V10: group starting with 10 mg PRED; and V60: group starting with 60 mg PRED). Primary analysis will be conducted by analysis of covariance (ANCOVA) for V60 versus Pl, using baseline values as covariates and 12-month values as dependent variables. In case of a statistically significant result (α = 0.05), a comparison of V10 versus Pl will be performed (α = 0.05). In case of superiority of V10 versus Pl, a non-inferiority test for V10 versus V60 will be performed (α = 0.025), as is shown in Figure 2. A non-inferiority margin of 1.3 SHS points has been selected.

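### The stated dose question is whether the regimens differ, but the only planned dose comparison is one-sided non-inferiority of V10, so there is no pre-specified confirmatory route to V60 being better

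*Protocol article*

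**What the plan says.** The Background section of the protocol article gives as one of two main aims "to define the best out of two standard GC dosage regimens", judged on one-year radiographic progression. The Discussion puts the second study question as "is there any difference between initially high and low PRED doses in the sense of benefit in radiographic progression". It also says that higher dosages may well have more effect on outcome. It qualifies the aim as "to test different treatment strategies rather than to evaluate the dose-dependent effect of PRED on the Sharp score".

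The section Blinding and statistical methods fixes three ordered steps:

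- Step one: "Primary analysis will be conducted by analysis of covariance (ANCOVA) for V60 versus Pl", at α = 0.05.
- Step two, if step one is significant: V10 against placebo, at α = 0.05.
- Step three, if V10 is superior to placebo: "a non-inferiority test for V10 versus V60 will be performed", at α = 0.025. "A non-inferiority margin of 1.3 SHS points has been selected".

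The Sample size section calls the step-three test one-sided and assumes equal progression on the two doses. The Discussion then interprets four outcomes: V60 not superior to placebo; V60 superior but V10 not; V10 comparable to an effective V60; and no differences among the three groups.

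**The concern.** A question about any difference, and an aim of finding the better regimen, can be answered in either direction. Step three looks in one direction only: whether V10 is not much worse than V60. If it fails, the formal result is that non-inferiority was not shown. That result does not separate a real V60 advantage from an estimate too imprecise to decide.

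The Discussion's list of interpretations has the same gap. Its only route to favouring V60 is V10 failing against placebo, which is not a comparison of the two doses. The outcome in which both doses beat placebo and non-inferiority is not shown has no entry. A reading chosen for that outcome after unblinding would not be confirmatory, although it bears on one of the two main aims.

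**Working it through.** **Inputs.** From Sample size: SD 7.5; effect versus placebo 3.7, or 3.5 after allowing for dropout; 150 per arm; margin 1.3; superiority two-sided at 0.05; non-inferiority one-sided at 0.025. Write δ for mean progression on V10 minus mean progression on V60, so a positive δ favours V60. Effects that differ between the doses are assumptions, because the plan gives none. All figures use the normal approximation.

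**The plan's own figures.**

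- Steps one and two: SE = 7.5 × √(2/150) = 0.866. Power = Φ(3.5/0.866 − 1.96) = 0.98, which agrees with the stated >0.95.
- Step three: SE = 7.5 × √(2/149) = 0.869. Power at δ = 0 is Φ(1.3/0.869 − 1.96) = Φ(−0.46) = 0.32, not the stated >0.80. An SD of about 4.0 returns 149 per group, but the article does not state that SD. This is a separate point. It matters here because it makes the uninterpreted outcome common, so results at SD 4.0 are shown where available.

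**Error rate of a two-way reading.** Non-inferiority rejects δ ≥ 1.3 and V60 superiority rejects δ ≤ 0. No δ satisfies both nulls, so at most one is true and at most one can be falsely rejected, with probability at most 0.025. In simulation with equally effective doses, false V60 superiority after steps one and two occurred in 2.1% to 2.5% of trials. Declaring both would need an interval inside 0 to 1.3. The interval half-width is 1.96 × 0.866 = 1.70 at SD 7.5 (full width 3.40) and 0.91 at SD 4.0 (full width 1.82). Both exceed 1.3, so the two declarations do not coincide at either SD.

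**What the added reading yields.** Three arm means were simulated with SD 7.5 and 150 per arm. The first column gives the true effects versus placebo.

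| V60 / V10 | Steps 1 and 2 pass | and V10 non-inferior | and V60 superior (added) |
|---|---|---|---|
| 3.7 / 3.7 (plan) | 98% | 31% | about 2% (false positive) |
| 3.7 / 3.0 | | | 10% |
| 3.7 / 2.5 | | | 18% |
| 3.7 / 2.4 | | | 20% |
| 3.7 / 1.85 | | | 25% |
| 4.5 / 2.5 | 82.3% | 0.3% | 47.9% |
| 5.0 / 2.5 | 82.3% | 0.04% | 65.1% |

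Blank cells are not needed for the argument. At 5.0/2.5 the plan as written leaves 82.3% − 0.04% ≈ 82% of trials with both doses superior and no dose conclusion; the added reading resolves 65 of those 82 points. At 4.5/2.5 it resolves 48 of 82. Under the plan's own assumption of equal doses, 98% − 31% = 67% of trials fall in the same outcome, and the added reading rightly resolves almost none of them. At an assumed SD of 4.0, effects of 4.5/2.5 would show V60 superior in 99% of trials.

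**The case against.** **A reader might infer that the trial can never conclude that V60 is better.** The documents do not support that. A one-sided 0.025 test corresponds to a two-sided 95% interval, and an interval wholly above zero would favour V60. Nothing in the plan forbids looking at it. What is missing is a pre-specified confirmatory status for that reading.

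**A reader might also take 65% or 48% as the expected gain.** Those figures set V60 at 5.0 or 4.5, above the plan's 3.7. With V60 at 3.7 the gain is 10% to 25%. Under equal doses the unresolved outcome comes from imprecision, not from the missing reading.

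**The aim is about strategies.** The Discussion disclaims a dose-dependent effect, and the article reports that most departments avoid 60 mg because of toxicity concerns. Asking whether the low dose suffices is therefore coherent, and non-inferiority is a legitimate choice. But the Discussion goes on to define the strategy aim by two questions, and the second is the high-versus-low comparison. The wording claims more than the test delivers.

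**Unseen documents.** Figure 2, the full protocol and any SAP are not shown, so a further step there cannot be excluded. The article nevertheless sets out its hierarchy as three steps, in the abstract and in the methods, and interprets that hierarchy. The mismatch is between a stated aim and a stated test.

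**The general caveat.** The Discussion accepts that uncertainty may remain and that a confirmatory trial may be needed. That is fair, but it assigns no reading to this outcome.

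**Missing data.** Step three excludes missing values, while steps one and two substitute placebo-group radiographs. A superiority claim at step three would rest on complete cases. This objection stands and is taken into the fix.

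**Conclusion.** The point holds in this form: when both doses beat placebo, the stated procedure has no pre-specified confirmatory route to V60 being better on radiographic progression, and the Discussion has no interpretation for both doses superior with non-inferiority not shown. This rests on comparing the stated aim with the stated steps and needs no assumed effect.

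The size of the benefit does depend on assumptions. At SD 7.5 and 150 per arm it is about 10% to 25% of trials with V60 at 3.7 and V10 between 1.85 and 3.0, and about 48% and 65% at 4.5/2.5 and 5.0/2.5. It would be larger if the SD were nearer 4.0. The change does not cure the low precision of the dose comparison at SD 7.5. It is worth making because it costs almost nothing and closes a gap in a main aim.

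**What to change.** State in Blinding and statistical methods that, once steps one and two succeed, the two-sided 95% confidence interval for V10 minus V60 from the step-three model is read in both directions:

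- Upper limit below 1.3: V10 is non-inferior.
- Lower limit above 0: V60 is superior in radiographic progression.
- Neither: the dose question is unresolved. Add this outcome to the interpretations in the Discussion.
- Both, should precision allow it: V60 is better, by less than the margin.

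These are statements about the radiographic endpoint only. As the Discussion says, recommendations also weigh adverse events and other outcomes.

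Because step three excludes missing values, support any V60-superiority reading with a pre-specified missing-data sensitivity analysis. That small extra analysis is the downside. No alpha, patients or data are needed.

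If the investigators intend only to ask whether the low dose is sufficient, the alternative is to narrow the aim in the Background and the second question in the Discussion accordingly. The unlisted outcome would still need a stated reading.
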